### Study 2. Increasing sustained use of the CT program

The aim of this study is to test the effect of using a proactive approach (i.e. periodic e-mail prompting) on revisiting of the program compared to a reactive approach. Furthermore, the efficacy of these approaches with regard to behaviour change will be studied.

### Design

The second study consists of a randomized control trial (RCT) including one experimental group. A design with a baseline measurement and three follow-up measurements (6, 12 and 18 months) measuring health behaviour status, intention to change, cognitive variables and planning abilities, will be used to compare the experimental condition (use of a proactive technique) to a control condition (use of a reactive approach).

### Recruitment and procedure

The research sample consists of individuals that participate in the Dutch Adult Health Monitor and that decide to pay a first visit to the new CT program. After logging in to the program at baseline and consenting to participation by filling out an online informed consent form, participants are randomly assigned to one of the two conditions. People in the experimental condition are reminded proactively via e-mail every three months for a period of 18 months to visit the CT program in order to obtain iterative feedback concerning their health behaviour status and additional CT advice, whereas people in the control condition do not receive any additional prompts and are only encouraged to re-visit the program in the future at baseline. All participants will be invited by e-mail for the follow-up measurements at 6, 12 and 18 months (Figure 2.).

**Figure 2 F2:**
[figure not shown]
**Flowchart study 2**.

### Inclusion and exclusion criteria for participants

Participants can be included in the current study when they are between 18 and 65 years and able to understand the Dutch language sufficiently. Moreover, they have to have access to the Internet. There are no explicit exclusion criteria stated for the current study.

### Materials

Three months after their first visit, participants in the experimental condition receive an e-mail, prompting them to revisit the program. This e-mail opens with a personal salutation and reminds people about their first visit to the program. Also, in short, the content and purpose of the program will be summarized, in case people have forgotten about the details of the program. Subsequently, people are invited to revisit the program in order to obtain information on their current health status and to monitor their progress. Participants were also pointed out the opportunity to receive additional, iterative, health advice on the health behaviour selected at baseline or on a new behaviour. In order to facilitate logging in to the program, the e-mail will also contain details on personal log-in information (user name and password).

### Randomization

Interested participants are directed through the Adult Health Monitor to the new program, where they can log in to the program with a personal username and password. After signing in to the program, participants will be randomly allocated to either the control condition or the experimental condition. Randomization will occur at the respondent level by means of a computer software randomization device. Blinding of participants is not possible, since participants will take notice of the fact that they receive additional e-mail prompts or not.

### Outcome measures

The primary outcome measures are re-visits to the program and level of behaviour change. Program revisits are objectively monitored for a total period of eighteen months. Recordings will be done anonymously and will yield information about the number of times the program is visited, the duration of each visit (in minutes) and which specific behaviours are most frequently selected. Level of behavioural change is assessed by studying participants' adherence to public health guidelines set for these behaviours (0 = not complying with recommendations/1 = complying with recommendations).

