### Statistical analysis

#### Sample size and power

With regard to re-visits to the program (first primary outcome measure), it is estimated that approximately 50% of the respondents of the no-prompting condition will visit the site more often than four times (after the baseline, and the first three post tests after six, twelve and eighteen months). It is estimated that in the prompting condition 70% of the respondents will visit the site more than four times. Power calculations reveal that in order to be able to detect this difference with a power of 80% (p = .05) at least 186 persons per condition are needed. Taking into account potential attrition, it is proposed to collect the data of 250 persons per cell.

The second primary outcome measure is the level of health behaviour change. The current program entails a total of five health behaviours. Therefore, with regard to the assessment of behaviour change (second outcome measure), estimations for finding effects will be based on smoking, since this behaviour results in the most conservative power calculations. Approximately 25% to 30% of the population smoke [51]. Power estimations are based on the ability to detect a difference in quit rates of 10% with a power of .80 and a *p*-value of .05. It is estimated that, in order to detect this significant difference in quit rates, 219 smoking persons per cell are needed, resulting in a total of 438 smokers [52]. To be able to have 438 smokers in the sample (under the condition that 30% of the Dutch population smokes), 1575 participants need to be recruited. Accounting for 35% attrition during the trial period, the total sample size for this study will be approximately 4500 persons.

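### Study 2 sizes two primary outcomes at a full .05 each, and the second spans five behaviours with no test order, primary time point or joint-success rule

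*Protocol article*

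**What the plan says.** The Outcome measures section of Study 2 states: "The primary outcome measures are re-visits to the program and level of behaviour change". It scores behaviour change as a 0/1 variable for compliance with the public health guidelines. The sample size section calls the two outcomes first and second primary and adds: "The current program entails a total of five health behaviours". Smoking is picked there as the basis for the calculation because it is judged the most conservative; it is not named as the only behaviour to be tested.

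Both outcomes are sized at the same undivided level. For re-visits the plan says it can "detect this difference with a power of 80% (p = .05) at least 186 persons per condition are needed". For behaviour change the calculation is made "with a power of .80 and a *p*-value of .05".

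The Design section of Study 2 sets the timing: "A design with a baseline measurement and three follow-up measurements (6, 12 and 18 months"), with health behaviour status measured each time. The Analyses section plans logistic regressions on re-visits and on behaviour change. None of these sections ranks the outcomes for testing, divides the .05, names a primary follow-up or requires success on both.

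**The concern.** When two outcomes are both primary, each is tested at .05 and either may be claimed, the overall chance of a false-positive primary result exceeds 5%. It grows further if the second outcome is really five outcomes. A trial in which prompts do nothing could then report a benefit on a declared primary outcome, for instance on one of the five behaviours. Readers would take that as a confirmatory finding from a trial meant to inform how prompts are used in online lifestyle programmes.

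**Working it through.** **1. Is the .05 undivided?**

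Smoking: "Power estimations are based on the ability to detect a difference in quit rates of 10% with a power of .80". Only the difference is stated, so take 10% versus 20% as an assumption. With two-sided .05 and 80% power:
- n = (1.960·√(2·0.15·0.85) + 0.842·√(0.09 + 0.16))² / 0.10² = 199 per arm.
- With the continuity correction this becomes 219, which matches the protocol's 219 per cell.
- Sidedness is not stated. A one-sided .05 with 15% versus 25% gives 217, so the match is strong but not unique.

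Re-visits: the inputs are "approximately 50% of the respondents of the no-prompting condition will visit the site more often than four times" and "in the prompting condition 70% of the respondents will visit the site more than four times". At two-sided .05 and 80% power the formula gives 93 per arm, 186 in total. The printed 186 per condition therefore matches the two-arm total. That is a separate matter, but it too points to a full .05.

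**2. Error if each test is made at two-sided .05 and all null hypotheses are true**

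For k independent tests, the chance of any false positive is 1 − 0.95^k. The chance of one in favour of prompts is 1 − 0.975^k.

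| Tests | Either direction | Favouring prompts |
|---|---|---|
| 2 (re-visits, one behaviour measure) | 9.75% | 4.9% |
| 6 (re-visits, five behaviours, one time point) | 26.5% | 14.1% |

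Correlation lowers these. The ranges below come from multivariate-normal simulation (200,000 draws); the correlations are assumptions, since the article gives none.
- Two tests, correlation 0 to 0.8: 7.9–9.8% either way, 4.0–4.9% favouring prompts.
- Six tests, correlation 0 to 0.5 between behaviours and 0 to 0.2 with re-visits: about 22–27% either way, about 11–14% favouring prompts.

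The benchmark for the last column is 2.5%, which is what one two-sided test at .05 allows in that direction.

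**3. Power for smoking at the first Holm step, .05/5 = .01**

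Power = Φ[(0.10·√n − 2.576·√(2·p̄·(1−p̄))) / √(p₁(1−p₁) + p₂(1−p₂))], without continuity correction.

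The stated total of 4500, 35% attrition and 30% smokers give 4500 × 0.65 × 0.30 / 2 ≈ 439 smokers per arm.

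| Assumed quit rates | 219 per arm | 439 per arm |
|---|---|---|
| 10% vs 20% | Φ(0.36) = 64% | Φ(1.59) = 94% |
| 20% vs 30% | Φ(−0.16) = 44% | Φ(0.85) = 80% |

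For comparison, at .05 with 219 per arm the same formula (1.960 in place of 2.576) gives 84% for 10% versus 20%. For 20% versus 30% it gives Φ[(1.480 − 1.200)/0.608] = Φ(0.46) = 68%.

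**The case against.** The strongest reply is that this is a condensed article. Multiplicity handling, the primary time point and the repeated-measures model are often left to an analysis plan, which is not shown here, and a .05 in a sample-size paragraph does not by itself set a rule for declaring success. That is fair, and the absence of a multiplicity section is not the point. The choice of two primaries, the breadth of the second and the level at which each is powered are stated in the article. Splitting the .05 later would change the power claimed there: at 219 smokers per arm and .05/6 per test, power for 10% versus 20% falls from 84% to about 62%.

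A second reply is that requiring success on both outcomes would need no adjustment. That is true, but no such rule is stated. The Discussion treats behaviour change as a possible addition to an effect on sustained use.

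A reader might infer more than the text supports, in four ways:
- **Sixteen primary tests, with 56% error (1 − 0.95^16).** The article lists three measurement times, not fifteen behaviour tests, and one longitudinal model per behaviour would leave six tests.
- **A false claim for prompts well above 5% from the two named outcomes alone.** In that direction two tests give just under 5%; the larger figures depend on testing five behaviours.
- **Any single significant result would trigger the recommendations on prompts.** The Discussion makes sustained use the condition, so an isolated behaviour result would not meet it, though it would still be a claim on a primary outcome.
- **Behaviour change can come only through extra visits.** The Discussion says repeated exposure makes it more likely, not that this is the sole route.

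**Conclusion.** The concern holds in a bounded form and should be addressed. With re-visits and five behaviours each tested at two-sided .05 at one time point, the chance of at least one false-positive primary result is about 22–27%, or about 11–14% in favour of prompts. This rests on reading the second primary as five separate compliance outcomes, which is the natural reading because no composite is defined, and on the assumed correlations. If behaviour change were one overall measure, the figures would be 9.8% and just under 5% with independent tests. Separate testing at three follow-ups would increase the error, but the article does not commit to it.

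**What to change.** Fix the order of testing before outcome data are seen, following the protocol's own labels of first and second primary:

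1. Test re-visits over 18 months at .05.
2. Only if that is significant, test guideline compliance at 18 months, with Holm's procedure over the five behaviours.
3. Report the 6- and 12-month results as supportive.

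This holds the overall error at 5% and takes nothing from the re-visit test. It needs one paragraph.

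There are two costs. First, no confirmatory behaviour claim is possible if re-visits are not significant. Under the protocol's own 50% versus 70% this risk is small: power is over 99% at the 250 per arm it proposes for this outcome. Second, smoking may have to pass .01, where 219 smokers per arm give about 64% power (10% versus 20%) or 44% (20% versus 30%). With about 439 per arm the figures are about 94% and 80%.

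The better figures require that the stated 4500 is actually recruited. That total does not follow from the section's own inputs: 1575/0.65 is about 2424, which would leave only 2424 × 0.65 × 0.30 / 2 ≈ 236 smokers per arm. The sponsor should confirm the target before relying on it.

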### Secondary outcome measures

Secondary outcome measures include overall tobacco use (number of cigarettes/day), level of physical activity (minutes/day), and overall level of fruit (pieces/day), vegetables (grams/day) and alcohol consumption (glasses/day). Furthermore, socio-cognitive measures, such as intention, attitude, social influence, self efficacy, action and coping planning will be measured.

### Statistical analysis

#### Sample size and power

With regard to re-visits to the program (first primary outcome measure), it is estimated that approximately 50% of the respondents of the no-prompting condition will visit the site more often than four times (after the baseline, and the first three post tests after six, twelve and eighteen months). It is estimated that in the prompting condition 70% of the respondents will visit the site more than four times. Power calculations reveal that in order to be able to detect this difference with a power of 80% (p = .05) at least 186 persons per condition are needed. Taking into account potential attrition, it is proposed to collect the data of 250 persons per cell.

The second primary outcome measure is the level of health behaviour change. The current program entails a total of five health behaviours. Therefore, with regard to the assessment of behaviour change (second outcome measure), estimations for finding effects will be based on smoking, since this behaviour results in the most conservative power calculations. Approximately 25% to 30% of the population smoke [51]. Power estimations are based on the ability to detect a difference in quit rates of 10% with a power of .80 and a *p*-value of .05. It is estimated that, in order to detect this significant difference in quit rates, 219 smoking persons per cell are needed, resulting in a total of 438 smokers [52]. To be able to have 438 smokers in the sample (under the condition that 30% of the Dutch population smokes), 1575 participants need to be recruited. Accounting for 35% attrition during the trial period, the total sample size for this study will be approximately 4500 persons.

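### The 186 persons per condition given for 50% versus 70% re-visiting at 80% power matches the total for both arms; the per-condition figure is 93

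*Protocol article*

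**What the plan says.** The point concerns the protocol article, Study 2, under Sample size and power. For re-visits, the first primary outcome, the planning rates are that "approximately 50% of the respondents of the no-prompting condition will visit the site more often than four times" and that "in the prompting condition 70% of the respondents will visit the site more than four times". The requirement follows: "power of 80% (p = .05) at least 186 persons per condition are needed". The next sentence raises that number: "Taking into account potential attrition, it is proposed to collect the data of 250 persons per cell". No attrition rate, inflation method, test, sidedness or allocation ratio is given for this outcome.

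The following paragraph sizes the second primary outcome on smoking. There it separates the two quantities, giving 219 smokers per cell and 438 in total. It ends: "Accounting for 35% attrition during the trial period, the total sample size for this study will be approximately 4500 persons".

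**The concern.** A sample size statement fixes four things together: the two rates, the significance level, the power and the number per arm. Here the first three do not lead to the fourth. A 20-point difference around the middle of the scale is large, and 186 per arm is about twice what it normally requires at 80% power.

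What is at stake is the accuracy of the published justification for a primary outcome. A reader planning a similar prompting trial would take over a requirement twice as large as these assumptions imply. A reader judging this trial would take its power for re-visits to be far lower than the stated numbers give.

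**Working it through.** **Inputs.** From Sample size and power: control rate p1 = 0.50, prompting rate p2 = 0.70, significance level 0.05, power 80%. The Recruitment and procedure section of Study 2 says that "participants are randomly assigned to one of the two conditions". Two inputs are assumed: a two-sided test, and 1:1 allocation, because a single per-condition figure is given.

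**Step 1: the plan's own figure.** With mean rate 0.60 and difference 0.20, the pooled-variance normal approximation is

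n per arm = [1.96 × √(2 × 0.60 × 0.40) + 0.8416 × √(0.50 × 0.50 + 0.70 × 0.30)]² / 0.20²

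= [1.96 × √0.48 + 0.8416 × √0.46]² / 0.04 = 93.0.

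This is 93 per condition, and 2 × 93 = 186 in total. The printed number is reproduced exactly, but as a total.

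**Step 2: other formulas.** Could a different method give 186 per arm at 80% power?

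| Method | Per condition | Total |
|---|---|---|
| Two-sided, pooled | 93 | 186 |
| Two-sided, continuity-corrected | 103 | 206 |
| Two-sided, unpooled | 91 | 182 |
| Two-sided, arcsine | 93 | 186 |
| One-sided, pooled | 74 | 148 |
| One-sided, continuity-corrected | 83 | 166 |

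None does. Halving the significance level to 0.025 for two primary outcomes gives 113 per condition, and a level of 0.01 gives 139. Raising the power to 95% at 0.05 gives 153. To need about 186 per condition at 80% power, the prompting rate would have to lie between 64.25% (189 per condition) and 64.5% (182), not at 70%.

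**Step 3: power at the stated sizes** (50% versus 70%, two-sided 0.05).

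Power = Φ{[0.20 × √n − 1.96 × √0.48] / √0.46}

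| Per condition | Power |
|---|---|
| 93 | 80.0% |
| 186 | 97.8% |
| 250 | 99.6% |
| 162.5 (250 less 35%) | 96.1% |

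**Step 4: the step from 186 to 250.** With no rate stated, the implied rate depends on the method.

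- Dividing by the retained fraction: 1 − 186/250 = 25.6% loss.
- Multiplying up by 35%: 186 × 1.35 = 251, which is 250 within rounding.
- For comparison, 35% loss by division would give 186/0.65, or 287 per condition; starting from 93 it would give 93/0.65, or 144.

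**The case against.** The strongest reply is that nothing depends on this. The text says that at least 186 are needed, and 186 is more than enough. Even 250 per cell less 35% keeps 96.1% power, and the total of about 4500 is set by smoking. That stands, and it is why the severity is low. It does not make the sentence correct, because 80% power and 186 per condition cannot both hold at 50% versus 70%.

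A second reply is that the cause is inferred, since the article gives no formula, sidedness or software. This also stands. The mismatch is shown by arithmetic; the mislabelled total is only its likely explanation, supported by the exact match at 2 × 93.

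A reader might infer three stronger points, which the article does not support:

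- **That 250 per cell contradicts the 35% attrition.** No rate is stated for the 250. It implies 25.6% by division but fits 35% if multiplied up. Nor is the smoking calculation a clean benchmark: 1575/0.65 = 2423, whereas the stated 4500 equals 1575/0.35.
- **That this outcome needs no attrition allowance because log-in data are complete.** The article does say "Program revisits are objectively monitored for a total period of eighteen months", but not that every randomised person's record will be complete. Its Analyses section also puts baseline cognitions in the models. These come from an additional tailoring questionnaire, so the analysable number could fall below the number randomised.
- **That the allowance means non-returners will be left out of the re-visit analysis.** Nothing in the Outcome measures, Sample size or Analyses sections says so. Analysis sets commonly belong to a full protocol or analysis plan, which is not at hand.

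**Conclusion.** The stated per-condition requirement for the first primary outcome does not correspond to the stated power. At 50% versus 70%, two-sided 0.05 and 1:1 allocation, 80% power needs 93 per condition, or 103 with continuity correction. The figure of 186 is therefore twice the per-arm requirement and was probably meant as the total.

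The conclusion rests on the assumed two-sided test and equal arms, but a one-sided test would only widen the gap. The error overstates the requirement, so it leaves the trial oversized for re-visits rather than underpowered. With about 4500 participants, even a 35% loss leaves 4500 × 0.65 / 2 = 1462.5 per arm, where power for this difference is practically 100%. No recruitment target, test or conclusion changes. On attrition, what can be said is limited: the 250 per cell comes without a rate or a method, so it cannot be checked.

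**What to change.** In Sample size and power, do one of the following:

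- write 93 per condition (186 in total) for 80% power; or
- keep 186 per condition and state the power as about 98%.

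Name the test, its sidedness, the allocation ratio and whether a continuity correction was used (with one, the figure is 103 per condition).

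Then restate the 250 per cell so that it follows from the corrected number, giving the attrition rate and whether it was applied by dividing by the retained fraction or by multiplying up. If 186 becomes the total, also say whether 250 is still meant per cell.

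The cost is a change of text in one paragraph. The planned total, the design and the analyses are unaffected.

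### The Study 2 total of about 4500 does not follow from the stated 438 smokers, 30% prevalence and 35% attrition

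*Protocol article*

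**What the plan says.** Everything needed is in one paragraph of the Protocol article, Study 2, under Sample size and power.

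- The behaviour-change outcome, the second of two primary outcomes, is sized on smoking. The aim is to "detect a difference in quit rates of 10% with a power of .80" at a p-value of .05. The base quit rate is not given.
- The result is "219 smoking persons per cell are needed, resulting in a total of 438 smokers".
- Background prevalence: "Approximately 25% to 30% of the population smoke".
- Conversion to participants: "under the condition that 30% of the Dutch population smokes), 1575 participants need to be recruited".
- Final step: "Accounting for 35% attrition during the trial period, the total sample size for this study will be approximately 4500 persons".

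No other inflation factor is named for the last step. The Study 2 section on recruitment and procedure confirms two arms: "participants are randomly assigned to one of the two conditions".

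**The concern.** Each step is a single division, and two of them do not give the printed result. The first gap is small. The second nearly doubles the total.

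The total of 4500 is the figure against which recruitment will be judged. As printed, two incompatible plans lie behind it. In one, the authors expect to lose about a third of participants and recruit almost twice as many as their own assumptions require. In the other, they expect to lose about two thirds, and the 35% is a misstatement. These say very different things about a primary outcome followed to 18 months, and they lead to different judgements if recruitment falls short. A trial that stopped at 2500, for example, would meet the requirement under the first reading at 30% prevalence and miss it badly under the second.

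**Working it through.** **Inputs (Sample size and power):** 219 smokers per cell, 438 in total; prevalence 30% for the conversion, 25% to 30% as background; attrition 35%; stated results 1575 and about 4500. Equal cells are assumed, as the figure of 219 per cell implies.

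**Step 0: smokers per cell.** The base quit rate is not stated. With 10% versus 20%, two-sided 5%, 80% power, the usual two-proportion formula gives 199 per cell. With continuity correction it gives 218.5, rounded up to 219. So 219 is reproduced, and 10% versus 20% is the working assumption for the power figures below.

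**Step 1: smokers to participants.** Participants = smokers / prevalence.

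- At the stated 30%: 438/0.30 = 1460.
- At 25%: 438/0.25 = 1752.
- Prevalence implied by 1575: 438/1575 = 27.8%.

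The printed 1575 is 1575/1460 = 1.079 times the correct figure, 7.9% too high for the condition that the sentence itself sets.

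**Step 2: attrition.** Recruited = analysable / (1 − attrition).

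| Starting figure | Divided by 0.65 (35% attrition) | Divided by 0.35 (65% attrition) |
|---|---|---|
| 1575 (as printed) | 2423 | **4500** |
| 1460 (30% smokers) | 2246 | 4171 |
| 1752 (25% smokers) | 2695 | 5006 |

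Other ways of applying 35% to 1575 also miss 4500: 1575 × 1.35 = 2126; 1575/0.65² = 3728; 1575/0.65³ = 5735. Treating 438 as the number per cell gives 876/0.30/0.65 = 4492, close to 4500, but the text says 219 per cell and 438 in total, and this route bypasses 1575.

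**Step 3: what 4500 delivers.** Smokers analysed = N × (1 − attrition) × prevalence.

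- 35% attrition, 30% smokers: 4500 × 0.65 × 0.30 = 877.5, about 439 per arm.
- 65% attrition, 30% smokers: 4500 × 0.35 × 0.30 = 472.5, above 438.
- 65% attrition, 25% smokers: 4500 × 0.35 × 0.25 = 393.75, below 438.

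Power for 10% versus 20%, compared like for like:

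| Smokers per arm | With continuity correction | Without |
|---|---|---|
| 219 | 80% | 83.7% |
| 439 | 98.3% | 98.6% |

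The figure depends on the base rate: without correction, 439 per arm gives about 93% for 20% versus 30% and about 88% for 30% versus 40%.

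**Step 4: what a total of 2250 would deliver if an assumption is wrong.**

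- 65% attrition, 30% smokers: 2250 × 0.35 × 0.30 = 236 smokers; power about 58% (50% with correction).
- 35% attrition, 25% smokers: 2250 × 0.65 × 0.25 = 366 smokers; power about 77% (72% with correction).

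**The case against.** The strongest reply is that the discrepancy is harmless because it enlarges the sample. On the printed inputs that is right: about 878 smokers would be analysed where 438 are needed. At 30% prevalence, even 65% attrition leaves enough. What remains is that the stated total is not the consequence of the stated inputs, and that at 25% prevalence with 65% attrition it would fall short.

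A second reply is that 1575 rests on a prevalence within the quoted 25% to 30%. That also stands. This gap is minor and errs towards a larger sample, although it contradicts the 30% condition in the same sentence.

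A third is that a journal article condenses a fuller protocol. That excuses omissions. Here the inputs and results are both printed and disagree, so the printed paragraph needs correcting whatever the full protocol contains.

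A reader might also infer that the authors certainly divided by the attrition rate in error, and that the sample should therefore be cut to about 2250. The document does not support this. The exact match of 1575/0.35 with 4500 fits a planned 65% attrition misprinted as 35% just as well, and Step 4 shows that 2250 would then be badly underpowered.

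**Conclusion.** The paragraph is wrong as written. The total of about 4500 cannot be obtained from 438 smokers, 30% prevalence and 35% attrition, which require about 2246; the printed intermediate of 1575 requires 2423, and the lowest quoted prevalence 2695. The stated total is thus about 1.7 to 2.0 times the requirement (4500/2695 to 4500/2246). The mismatch is a matter of arithmetic; its cause is not established.

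It does not follow that the trial is underpowered for smoking. On the printed inputs it is overpowered relative to the stated 80%: about 98% with continuity correction, assuming 10% versus 20% quitting. The shortfall at 65% attrition and 25% smokers depends on two assumptions that the article does not state together. The main damage is that N, attrition and power cannot all be true at once, and a reader cannot tell which one to distrust.

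**What to change.** First state which attrition and which prevalence were intended; no total should be restated before that. Then make the chain consistent.

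- **If 35% attrition is right:** the requirement is about 2250 at 30% smokers and about 2700 at 25%. It helps to give the target also as smokers randomised, 438/0.65 = 674, which does not depend on prevalence. If 4500 is nevertheless kept, restate the power as about 98% for 10% versus 20% quitting with continuity correction, and state the base quit rate.
- **If 65% attrition was meant:** correct the 35%, and note that 4500 covers the need at 30% smokers (4171) but not at 25% (about 5006).
- **In either case:** replace 1575 by 1460, or state the prevalence of about 27.8% that it reflects.

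The cost is one rewritten paragraph. Recruitment need not change if 4500 is kept and 35% attrition or 30% smokers holds. Protecting against 65% attrition together with 25% smokers would take about 500 more participants (5006 − 4500 = 506).
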